### Data collection: Instruments

***Phases 1 and 2***: Several instruments will be used for data collection. The variables related to the fall and older person will be collected through the fulfilment of a specific record sheet for falls. This record sheet will have to be completed by the patient’s referring nurse (professional who generally records the fall, a fact documented in previous investigations [6]. The registration sheet will be the one attached at the end of this report, similar to that used in a previous project of the research group [20] (ANNEX I). To facilitate this process, an electronic data collection notebook will be hosted on the website of the study hospitals.

On the other hand, the sleep pattern will be measured by means of the Pittsburgh Sleep Quality Index (Spanish version) [29]. The chronotype of each person will be determined using the Horne-Östberg Morningness-Eveningness Questionnaire (Spanish version) [30]. For the quality of life related to health, the 36-Item Short Form Health Survey, version 2 (SF-36v2) (Spanish version) will be used [31], while for the general health status, the 28-Item General Health Questionnaire (GHQ28) (Spanish version) will be used [32]. The variables somnolence, fatigue and speed of response to the event will be measured by means of the Epworth Sleepiness Scale (Spanish version) [33].

With the intention of managing the data appropriately, an electronic data collection notebook will be developed by the Bioinformatics Unit of the Maimonides Institute for Biomedical Research of Córdoba.

***Phase 3***: The focus groups will be constituted with healthcare professionals—doctors, nurses and nursing assistants who provide and have provided their professional services in the field of study in the period previously indicated.

### Data collection: Procedure

***Phase 1***: The project will be explained to the institutional managers of the centres included in the study, who will appoint a coordinator to ensure proper development and will work in coordination with the research team. In these meetings, the process of recording falls will be disclosed, as well as the other variables.

Prior to data collection, meetings will be held with those responsible for the Clinical Management Units and special mention will be made of the areas that are expected to have a greater number of events (internal medicine, neurology, trauma, rehabilitation, …). Additionally, the dynamics of data collection will be explained.

On the other hand, being focused more on healthcare professionals (especially nurses) from the different study centres, several seminars will be held (first intervention), explaining how data collection should be done, as well as the definition of variables included in the record sheet. Such seminars will be proportional to the number of workers in the different centres included, being distributed over different days so that the number of workers receiving information is as large as possible. In addition, specific audits will also be carried out in each Clinical Management Unit.

During the first 18 months of study development, each time a fall occurs, in addition to recording the circumstances of the fall, it is necessary to obtain the informed consent of the patient to know their quality of life, general functional status, sleep pattern and chronotype. In healthcare professionals, informed consent must also be obtained to know the previous variables, as well as the values of fatigue/sleepiness, attention and cognitive functionality. In this sense, as it has been commented on in the inclusion/exclusion criteria, these variables will only be known in the healthcare professionals responsible for the older person, who have visualized and/or attended the fall event, even though the fall may be the result of a collective lack of attention from all the staff and not from a single person.

Once the prospective data collection period has started (January 2018), monthly individualized audits will be carried out in the different Clinical Management Units, aimed at managing correct data collection. Furthermore, these audits will allow obtaining a perspective of the fall event in relation to the number and related circumstances.

After obtaining and analysing the falls that occurred during the first 18 months of the study, time-adjusted preventive measures will be carried out. These measures will be focused on organizational, educational and behavioural elements (previously mentioned).

The establishment of the programme of time-adjusted prevention measures will be carried out in May 2019 in the four centres. The post-intervention data collection will cover July 2019 to September 2020. The managers responsible for each centre, together with the research team, will implement the measures, and, as in the first phase, seminars will be held with healthcare professionals to focus on the recording of falls and their circumstances, as well as the variables included in the prevention programme.

During the post-intervention phase, the individual monthly audits will continue to be carried out with each Clinical Management Unit. This follow-up will make it possible to discern the effectiveness of the preventive measures.

***Phase 2***: For the retrospective study, the data will be delivered by the centres participating in the project to the Principal Investigator anonymized.

***Phase 3***: The development of the focus groups will be carried out in the facilities of the participating hospitals, ensuring the confidentiality of the participants. Four focus groups will be held at the Reina Sofia University Hospital in Córdoba and one in each of the three regional centres.

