## Methods/design

### Aims

The main aim of this study will measure the effect of the implementation of a falls prevention programme based on temporal patterns and relative risks factors.

Secondary aims will be: (i) to identify temporal patterns in the incidence of hospital falls and intrinsic and external risks factors, pre- and post-intervention; (ii) to establish differences in temporal patterns according to the hospital setting (teaching or non-teaching) and the different types of wards (medical, surgical or mixed), pre- and post-intervention; (iii) to study the role of circadian time in drug administration for older people suffering from hospital falls, pre- and post-intervention; (iv) to identify the level of fatigue/sleepiness, attention and cognitive functionality of healthcare professionals intervening during hospital falls, pre- and post-intervention; and (v) to develop a uniform, simple and intuitive method to record hospital falls in order to improve the effectiveness of the registration of falls and to assess the implementation pre- and post-intervention.

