### Design

A mixed-method research design will be carried out. Three different study designs will be used:

***Phase 1.*** Prospective longitudinal study in two steps:

A first step of 18 months, in which a first intervention of audits and seminars in healthcare professionals will be carried out, focused on an effective and efficient registry of hospital falls in older people. This first phase is crucial to identify temporal patterns of falls in relation to specific intrinsic and extrinsic risk factors among hospitalized older people, as well as the levels of fatigue/sleepiness, attention and cognitive functionality of the healthcare professionals who attend to an in-hospital fall.A second step of application of a multidimensional prevention programme for 15 months focused on organizational, educational and behavioural elements applied to admitted older people and healthcare professionals.

***Phase 2.*** Retrospective study of the fall records found in the institutional databases of the study centres in the period between January 2018 and September 2020. This period covers the first (January 2018–May 2019) and second phases (June 2019–September 2020) of the project, as previously indicated.

***Phase 3.*** Descriptive exploratory study with a qualitative approach, focus groups made up of healthcare professionals: doctors, nurses and nursing assistants who provide and have provided their professional services in the field of study, in the periods in which the longitudinal and retrospective studies have been carried out.

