### Inclusion and exclusion criteria

***Phase 1.*** Regarding patients, they should have been admitted in the aforementioned hospitals, should be over 65 years old and suffer an in-hospital fall. Furthermore, they should sign an informed consent accepting to participate in the study.

Healthcare professionals should have the following requirements: to sign an informed consent accepting to take part in the study and to be nurses in charge of the care of older people suffering from hospital falls, despite not witnessing the event.

Patients who suffer from hospital falls and healthcare professionals who take care of them will be included in the study continuously, which means after every single fall event.

In both cases (patients and healthcare professionals), the sampling will be total.

***Phase 2.*** Records of falls suffered in patients over 65 years old collected in different institutional databases (adverse event report, clinical record of the patient…) in the four hospitals. As in phase 1, the sampling will be total.

***Phase 3.*** Selection of healthcare professionals will be intentional and with the leverage of the collaboration with the centres involved. One person for each sector (doctors, nurses and nursing assistants). Inclusion criteria will be: (i) healthcare professional who has worked in the four hospitals during the time the longitudinal study is carried on; (ii) professionals of clinical units where hospital falls will be recorded during the longitudinal study; and (iii) professionals of clinical units in that are important to the risk of in-hospital falls, by pathologies, dependence, motor or mobility disorder, etc.

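### The article disagrees with itself on whether the staff measures for aim (iv) continue after month 18, and it assigns a sleepiness questionnaire to fatigue and speed of response

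*Protocol article*

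**What the plan says.** **Aim.** Aim (iv) concerns healthcare professionals only, and it is explicitly a two-period aim: "to identify the level of fatigue/sleepiness, attention and cognitive functionality of healthcare professionals intervening during hospital falls, pre- and post-intervention".

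**Timing, first-step text.** Under Design, the 18-month first step is said to be needed for the fall patterns, "as well as the levels of fatigue/sleepiness, attention and cognitive functionality of the healthcare professionals who attend to an in-hospital fall"; the sentence on the 15-month second step does not mention these measures. Study variables lists them under Step 1, before the preventive measures, and not under Step 2. Data collection: Procedure opens its paragraph on patient and staff measurements with "During the first 18 months of study development, each time a fall occurs". It then says that consent is also needed from professionals for the same variables, "as well as the values of fatigue/sleepiness, attention and cognitive functionality".

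**Timing, whole-study text.** Participants and setting includes the reference nurses, for exactly these variables, for falls in the study period, which for Phase 1 is January 2018 to September 2020. Inclusion and exclusion criteria says that patients and professionals enter continuously, after each fall, and gives no stop at month 18.

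**Instruments.** "The variables somnolence, fatigue and speed of response to the event will be measured by means of the Epworth Sleepiness Scale". The same section assigns SF-36v2 to quality of life. In Study variables, quality of life for professionals includes a vitality and fatigue component. No instrument is named under attention or cognitive function.

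**Which nurse.** The inclusion criteria take the nurse in charge "despite not witnessing the event". The Procedure limits the measures to responsible professionals "who have visualized and/or attended the fall event".

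**The concern.** Aim (iv) needs the same measures in the same kind of nurse in both periods. The section that tells sites what to do after a fall ties those measures to the first period, while the eligibility sections do not. A site following the Procedure could stop seeking staff consent and questionnaires after month 18; a site following the eligibility text would carry on. With four hospitals, this could also produce uneven post-intervention data by centre.

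The contrast has some substance. The prevention programme includes changes to how staff shifts are distributed, which could plausibly alter fatigue. The background section on chronoprevention argues that fatigue, attention and cognitive function affect vigilance to falls and have to be evaluated.

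The instrument sentence is a separate problem. Followed as written, it would put a sleepiness score under the labels of fatigue and speed of response.

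**Working it through.** **1. The plan's own calendar.** Inputs: 18-month and 15-month steps (Design); January 2018 to September 2020 (Participants and setting); post-intervention collection July 2019 to September 2020 (Procedure).

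- Total: 12 (2018) + 12 (2019) + 9 (2020) = 33 months. The steps give 18 + 15 = 33, so the plan's lengths are reproduced.
- First 18 months: 12 (2018) + 6 (2019), ending June 2019.
- Post-intervention window: 6 (July to December 2019) + 9 (2020) = 15 months.

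**2. Post-intervention months with staff measures, by reading.**

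| Governing text | Post-intervention months covered |
|---|---|
| Procedure, taken literally (first 18 months) | 0 of 15 |
| Participants and Inclusion sections (whole study period) | 15 of 15, 33 months in all |

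The Phase 2 paragraph of Design divides the project differently: January 2018 to May 2019 (12 + 5 = 17 months) and June 2019 to September 2020 (7 + 9 = 16 months). On that division, the literal Procedure reading covers 1 of 16 second-phase months, June 2019. The conclusion does not change.

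**3. Constructs against instruments.**

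| Construct | In aim (iv)? | Instrument in the article | Suitable? |
|---|---|---|---|
| Sleepiness | yes | Epworth Sleepiness Scale | yes |
| Fatigue | yes | Epworth; also within SF-36v2 quality of life | Epworth no; SF-36v2 vitality available |
| Attention | yes | none named | not assessable here |
| Cognitive function | yes | none named | not assessable here |
| Speed of response | no | Epworth | no; a questionnaire does not time an event |

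The judgement on the Epworth scale needs only its name and its use here as a questionnaire.

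**4. Nurse definition.** Take a nurse in charge of a patient who falls:

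- saw the fall: included under both sections;
- did not see it but attended afterwards: included under both;
- neither saw nor attended it: included under the inclusion criteria, left out under the Procedure.

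The definitions differ only in the third case. The article gives no figure for how common it is.

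**The case against.** The strongest objection concerns timing. A reader might infer that aim (iv) cannot be met and that no post-intervention staff data will exist. The documents do not support that as a flat statement. Participants and setting names these same variables and enrols nurses for the whole study period, and the inclusion criteria add continuous entry after every fall. The Procedure paragraph is framed around consent and does not say that collection ends at month 18. It is also tempting to read the post-intervention paragraph as listing only falls, circumstances and programme variables. That sentence describes the focus of the seminars; the sentence giving the collection dates restricts no variables. What stands is a contradiction, since three sections place the staff measures in the first step only.

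On instruments, a reader might infer that a sleepiness score will be presented as attention or cognition. The article does not assign the Epworth scale to either, and a condensed article may leave those instruments to the full protocol. Their absence is therefore not itself an error. Speed of response is not part of aim (iv), and fatigue has another measure in SF-36v2. What stands is the sentence as printed: assigning a sleepiness scale to fatigue and response speed is a positive misstatement that condensation does not explain.

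Two further limits are accepted. The patient questionnaires in the same Procedure paragraph are irrelevant to aim (iv), and the nurse-definition gap is narrow.

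**Conclusion.** The point holds as a conflict to reconcile plus one wrong instrument assignment. Post-intervention coverage of the staff measures ranges from 0 of 15 months (Procedure taken literally) to 15 of 15 (eligibility sections); the article does not settle which applies. At the lower end, the pre/post part of aim (iv) has no estimate, although the pre-intervention level can still be described.

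On measurement, sleepiness is covered and fatigue can be recovered from SF-36v2. Speed of response is not measured by the scale assigned to it. Whether attention and cognitive function are measured cannot be judged without the full protocol.

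This affects one of five secondary aims. The main aim and the falls outcome are untouched. It should be corrected, but it does not threaten the study's principal result. The month counts rest on inclusive calendar months and the July 2019 start given in the Procedure.

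**What to change.** 1. **Period.** In Data collection: Procedure, replace the opening limit in "During the first 18 months of study development, each time a fall occurs" with wording that covers both periods, January 2018 to September 2020, and name the staff measures under the second step in Design and Study variables as well. If post-intervention staff data were not in fact collected, restate aim (iv) as pre-intervention only.
2. **Instruments.** In Data collection: Instruments, report the Epworth score as sleepiness only, take fatigue from the SF-36v2 vitality domain already planned for staff, and drop speed of response. Make no claim on attention or cognitive function unless the full protocol names an instrument for them; if it does, cite it here.
3. **Nurse (minor).** Align the Procedure with the inclusion criteria: the nurse in charge at the time of the fall, whether or not a witness, with witness status recorded.

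The cost is wording, plus either the existing staff questionnaires continued for 15 more months or a narrower claim for this secondary aim.

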### Chronoprevention: a nursing intervention

To our knowledge, there are no epidemiological studies proposed with a chronobiological approach to demonstrate the influence of preventive counter-measures adjusted to temporal patterns on the incidence of accidental falls [28]. Therefore, it is necessary to develop prospective studies in order to confirm temporal patterns in hospital falls and to fully understand intrinsic and extrinsic risk factors.

Lastly, the temporal patterns of the professional team, including the number of qualified workers, the fulfilment of patient caring tasks and the characteristics of their work schedule, form another important factor to be considered during the examination of time patterns in accidental falls in hospitals.

Generally, healthcare worker teams are reduced in number during night shifts, weekends and holidays [21]. Some programmed tasks and activities of patient care have an influence on the progress of the fall, such as bed sheets changing, bathing, feeding or transferring [20].

Besides, the roles of fatigue/sleepiness, attention and cognitive functionality in healthcare professionals, just like disruptor agents of circadian time structure (i.e. shift work, night shift, etc.), could affect the vigilance and attention to falls during the day and night. Therefore, it is necessary to evaluate the aforementioned variables in order to define effectively and efficiently the aetiology of falls and, based on emerging temporal patterns, to implement preventive measures in order to reduce the occurrence of hospital falls.

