### Study variables

The main dependent variable will be the number of hospital falls. A hospital fall will be defined as “the consequence of a non-intentional and sudden movement towards the floor from a more elevated position” in hospital settings.

Other independent variables related with the patient who experiences a hospital fall include: (i) sociodemographic and economic data (age, gender, marital status and level of education); (ii) time (hour and minute, day and shift work) of fall; (iii) patient position (from the bed with or without bedrails, sitting, walking, and so on) and witness of the fall (roommate, family member, healthcare professional or no witness); (iv) use/no use of footwear and kind (open or closed); (v) cause of fall (instability (general instability and balance loss), dizziness (syncope, fainting and cardiovascular accident), drug adverse effects (diuretics, anti-hypertension and other drugs), accident (event with no identifiable cause), ambient-related (dropped objects, obstacles and wet floor), fragility (extreme fragility or weakness) or others); (vi) location of the fall (hospital room, bathroom, corridor, public area or others); (vii) fall-related injuries and severity (no wound/no consequences, minor wounds (grazes and minor contusions), afflicting wounds (contusions requiring stitches, fractures and skull trauma) or others (not afflicting wounds but still in need of minor medical intervention)); (viii) number and kind of coexisting clinical conditions; (ix) prescribed drugs and their time of administration; (x) chronotype measured by the Horne-Östberg Questionnaire (1976); (xi) quality of life in terms of body functionality, physical limitations, body pain, social role or function, mental health, emotional limitations, vitality, energy or fatigue and general perception about own health; and (xii) general health status in terms of somatic symptoms, anxiety, insomnia, social dysfunction and depressive symptoms.

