In the case of healthcare professionals, independent variables will be: (i) sociodemographic and economic data (age, gender, marital status, level of education, work experience and time worked in the unit); (ii) kind of contract and work unit; (iii) sleep pattern (quality and quantity of hours); (iv) chronotype measured by the Horne-Östberg Questionnaire (1976); (v) quality of life in terms of body functionality, physical limitations, body pain, social role or function, mental health, emotional limitations, vitality, energy or fatigue and general perception about own health; (vi) general health status in terms of somatic symptoms, anxiety, insomnia, social dysfunction and depression; and (vii) fatigue/sleepiness, attention and cognitive functionality.

Pre- and post-intervention will be:

***Step 1.*** Before implementing preventive measures: development of audits and seminars in order to improve, secure and control the registration of falls in hospitals and related factors, as well as others study variables (quality of life, functional status, chronotype, fatigue/sleepiness, attention and cognitive functionality). These interventions will be carried out by research nurses who are working in hospitals.

***Step 2.*** Implementation of a preventive measures programme: adjusted to the identification of temporal patterns of falls and relative risk factors of falls. As measures will be agreed with the managers of hospital centres, the interventions will be reflected in the official document of general objectives of the hospitals. Official document to which the personnel involved in the intervention have access. Preventive measures will be focused on organizational, educational and behavioural elements related to older people and healthcare professionals:

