## Discussion

In a multi-causal adverse event such as a fall, a good initial evaluation of hospitalized elderly people and their registration is necessary. The results of the study, in addition to stimulating the epidemiological investigation of falls, are intended to prevent falls in the hospital setting. Obtaining temporal patterns in hospital falls allows establishing high-risk periods during the day. This fact may correspond to certain activities predictable in time. In this sense, previous studies applied in Italian hospitals have shown that the establishment of time-adjusted preventive measures has led to a decrease in the number of falls [20, 21]. All this will contribute to improvement in the safety of the individual, and as consequence of their health, environment (family environment) and social level (due to the decrease in costs that a decrease in dependency implies) [20].

Furthermore, the study interventions emphasize the importance of recording in-hospital falls and their circumstances, especially time. Therefore, it represents a change in health policy. In previous studies [6], a low incidence of falls has been detected in the hospitals of Andalusia, being less than 1 %, although 65 year olds are the population that suffers the most from these types of events, which is contradictory. Contradiction contrasted with other studies [24], where healthcare professionals showed that there is an underestimation of hospital falls. On the other hand, the previous studies that support the present project [20] found high incidences as a result of an appropriate registry of these events.

Nurses routinely need 24 h per day to care for patients, in many different settings and environments. The impact on physical and psychological well-being of shift work management and lengths of shifts have been largely studied [36, 37]. The findings emerging from these investigations are that anomalies of the circadian rhythm summed with the characteristics of shift workers may have a direct influence on the health of nurses [38]. The outcome to be analysed in the proposed study relate chronotype, sleep quality and health status of the nurse with the quality of clinical practice and ultimately patient safety.

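### Patient health scores and nurse sleep, health and fatigue scores are collected only after a fall but listed as independent variables against the fall count, so direction cannot be established

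*Protocol article*

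**What the plan says.** All references are to the protocol article.

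- **Timing.** Under Inclusion and exclusion criteria, fallers and the nurses caring for them "will be included in the study continuously, which means after every single fall event". Under Data collection: Procedure, "each time a fall occurs, in addition to recording the circumstances of the fall, it is necessary to obtain the informed consent of the patient" for the quality-of-life, functional-status, sleep and chronotype measures. For staff, "these variables will only be known in the healthcare professionals responsible for the older person, who have visualized and/or attended the fall event".
- **Role.** Under Study variables, "The main dependent variable will be the number of hospital falls". The patient list opens with "Other independent variables related with the patient who experiences a hospital fall include" and includes quality of life as item (xi) and general health status, with anxiety, insomnia and depressive symptoms, as item (xii). The staff list opens with "In the case of healthcare professionals, independent variables will be" and includes sleep pattern, quality of life, general health, and fatigue or sleepiness.
- **Purpose, nurses.** The Background subsection on chronoprevention says that staff fatigue, attention and cognition "could affect the vigilance and attention to falls during the day and night", and asks for them to be evaluated so that the aetiology of falls can be defined. The Discussion plans to "relate chronotype, sleep quality and health status of the nurse with the quality of clinical practice and ultimately patient safety".
- **Purpose, patients.** The opening of the Background says hospital falls are a challenge because of what they do to patients' quality of life. The Abstract expects quality of life to improve alongside a reduction in falls.

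**The concern.** An independent variable offered as an explanation of an event should describe the person before the event. Here the event triggers the measurement. A patient who has been hurt or frightened may report more pain, less function, more anxiety and worse sleep because of the fall. A nurse whose patient has just fallen may report more anxiety or poorer sleep for the same reason.

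The stake is interpretation. Poor scores among fallers and their nurses could be presented as part of why falls happen. Injury severity is recorded too, so lower scores after injurious falls could be presented as a risk factor for injury. It also has a practical side: the second step of Phase 1 is to be shaped by the risk factors identified in the first, and the distribution of staff shifts is among its measures.

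**Working it through.** No arithmetic applies. The article gives no sample size, effect size or expected score for these measures, so the check sets timing against role.

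| Measure | When collected | Role in Study variables | Direction stated elsewhere |
|---|---|---|---|
| Patient quality of life, item (xi) | After the fall and consent | Independent | Background and Abstract: affected by falls |
| Patient general health, item (xii) | After the fall and consent | Independent | None specific |
| Nurse sleep, quality of life, general health | After a fall in the nurse's patient | Independent | Discussion (sleep quality, health status): towards patient safety |
| Nurse fatigue/sleepiness, attention, cognition | After a fall in the nurse's patient | Independent | Background: aetiology of falls |

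One reading is needed for the second row. The procedure text speaks of functional status where the variable list speaks of general health status, and I take these to be the same measure. If they are not, the timing still follows, because patients enter the study only after a fall.

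1. **Is there a pre-fall value?** None is described under Inclusion and exclusion criteria, either Data collection section, or Data analysis. No reference period for the answers and no maximum interval between fall and questionnaire is stated.
2. **Could the analysis restore direction?** Data analysis lists t tests, ANOVA, chi-square tests, Pearson correlation and logistic regression. Each measures association, and none can tell a score that preceded the fall from one altered by it. A statistical analysis plan could not create the missing pre-fall values.
3. **Would earlier timing be enough?** No. Every enrolled patient has fallen and every measured nurse cared for a patient who fell, so the indicator of a fall equals 1 for every record. With no non-fallers and no fall-free shifts, association with fall occurrence is not estimable even from perfectly timed scores. A score taken after a first fall does precede any second one, but that concerns recurrence among fallers, which no stated aim addresses.
4. **Is it acknowledged?** Limitations mentions unwitnessed falls and dependence on the professionals' own recording. It does not mention that scores may be consequences of the fall.
5. **Which measures are exposed?** State measures are most exposed: quality of life, general health, and sleepiness or fatigue. Chronotype is a fairly stable trait and is little affected.

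**The case against.** The strongest reply is that, for patients, the label is loose. The same list of independent variables contains injury severity, which is a consequence of the fall by definition, so the term may mean no more than other recorded variables. No aim names patient quality of life or mood as a predictor, and no model of falls or injury on these scores is written down. Secondary aim (iv), on nurses, is worded descriptively. All of this stands. A reader might infer that the protocol sets out to read patients' low mood or poor quality of life as a cause of falls; the documents do not go that far. What remains is that the role assigned to these scores conflicts with their timing and, for quality of life, with the article's own account of what falls do. For nurses the aetiological intent is explicit.

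Three other inferences should be resisted:

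- **A size in points.** The documents give no injury share and no effect of a fall on any score, so any such figure would be an assumption on top of an assumption.
- **Repeat testing.** A reader might conclude that a nurse completes the full set after every fall. The text requires consent and measurement at a fall, but does not say that a nurse already measured is tested again.
- **Look-back periods.** Questionnaire instructions or the annexed record sheet, which are not shown, might direct answers to an earlier period. That could soften the problem, but the answers would still be given after the event.

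**Conclusion.** The point holds as a mismatch between timing and role. All patient and nurse questionnaire scores follow the fall, the list of variables treats them as explanatory, and for nurses the article states an aetiological purpose. The direction of any association cannot be established, and association with fall occurrence cannot be estimated at all from fallers and their nurses alone.

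The reach is limited to secondary material. The number of falls does not depend on these questionnaires, and a description of nurses' levels at falls before and after the programme, as aim (iv) is worded, remains possible. The size of any bias is unknown. The conclusion assumes that no unpublished document provides for pre-fall measurement or a comparison group; nothing in the article suggests either.

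**What to change.** **Patients.** In Study variables, move items (xi) and (xii) out of the independent variables and call them post-fall characteristics or outcomes. Do not use them as predictors of falls or of injury severity in the planned tests and logistic regression. Alternatively, ask the questions explicitly about the period before the fall and report the answers as recalled. Reclassification needs no new data and can be done even after collection has ended. The recall option is imperfect, since an injured patient's memory of the earlier state may itself be coloured by the fall.

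**Nurses.** Keep every aim (iv) measure at the fall: fatigue or sleepiness, attention, and cognitive function. Report the post-fall sleep and health scores as descriptive, and drop the aetiological reading in the Background and the Discussion.

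**Optional, where feasible.** Also collect the chronotype, sleep-quality and health questionnaires at the seminars planned in both steps, and use the pre-fall value. This adds forms and consent for nurses who never attend a fall, and seminar attendance will not be complete. With steps of 18 and 15 months, a value taken once per step may be more than a year old at the fall, which is a weakness for changeable measures.

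**Statement to add.** Say in Data analysis or Limitations that, because only fallers and their nurses are measured, these scores cannot yield an association with fall occurrence.
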